### Study design

This study is an ongoing two-arm cluster-randomised controlled superiority trial (CRCT) with baseline and post-measurement. The study protocol follows the standard protocol for clinical trials according to the SPIRIT 2013 statement (Fig. 1; Additional file 2: SPIRIT checklist) [21].

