**Fig. 1 Fig1:**
[figure not shown]
SPIRIT figure

Primary schools are eligible to participate if (1) they are from one of the three federal states (North Rine-Westphalia, Rhineland-Palatinate, Schleswig–Holstein), (2) they have not implemented the MindMatters intervention in the past and (3) they agree to be assigned to either the intervention or control group. After enrolment, eligible schools will be randomly assigned 1:1 to either the intervention or control group using the Microsoft Excel random number function, with randomisation stratified by subgroups: federal state, school size, social gradient and level of activity in school health promotion. Within the subgroups, each school will be assigned a random number, with the proviso that, for example, schools with large random numbers will be assigned to the intervention group and schools with small random numbers will be assigned to the control group. Randomisation and communication with schools will be carried out by the investigators. Schools will be informed individually by e-mail of the outcome of the group allocation. Data will be collected at baseline and again 18 months after the start of the intervention, including the perspectives of pupils and teachers (both baseline and post-test) as well as parents (post-test only). While the MindMatters intervention is implemented in the intervention schools according to defined criteria, no intervention is implemented in the control schools. The trial flow of the evaluation study is shown in Fig. 2. The trial has been approved by the Ethical Review Board of Fulda University of Applied Sciences (Nr. 3.1.9.2), the Ministries of Education in Rhineland-Palatinate and Schleswig–Holstein, and registered with the German Clinical Trials Register (DRKS00023762).

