### Sample size calculation

In this study, schools represent the intervention clusters in which classes and pupils are nested. The power analysis relates to the individual pupil level, taking into account the cluster effect by including the intraclass correlation (ICC). There is no ICC estimate for mental disorders in the target age group, but it is estimated to be rather low compared to substance use or risky behaviour and is therefore set at *p* = 0.01 for the power analysis [22]. While the medium effects can be expected at the level of knowledge for primary school pupils (*d* = 0.5), small effects (*d* = 0.1 to 0.3) are assumed at the level of competence due to the short study period. Given the most recent findings on the prevalence, it is expected that the prevalence of mental health problems in the intervention group will be at most four percentage points lower than in the control group at the post-test.

Assuming an alpha level of 5% and a statistical power of 0.80, the estimated sample size is 2066 (with equal allocation to both groups, i.e. 1033 pupils in the intervention group and 1033 in the control group, https://www.sealedenvelope.com/power). Taking into account an intra-class correlation of 0.01 and a number of approximately 15 pupils per class with parental consent and actually present on the day of the survey, the required total sample size increases as follows: (1 + (15 − 1) × 0.01) × 2066 = 2355. Based on previous studies in primary school education, an attrition rate of about 10% is calculated for the pre-post survey at the pupil level across the different measurement points, so that a total sample of 2615 pupils from 174 classes is required for the baseline test. It is planned to implement this with a total of 40 participating primary schools (20 in the intervention group and 20 in the control group).

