### Measures

The intervention model includes a set of outcomes that unfold gradually in the short-, medium- and long-term levels and can be observed at the school and individual levels (mainly pupils and teachers, Additional file 3: MindMatters intervention model for primary schools) [23]. The primary outcome of this study includes several indicators of pupils’ mental health (e.g. emotional symptoms, conduct problems, prosocial behaviour). According to Nutbeam’s outcome model, these effects are preceded by direct effects at the individual level, such as knowledge or skills, but also at the classroom and organisational levels, such as classroom climate, classroom disruption, integration of health promotion into the school mission or organisational commitment. In line with the basic assumption of the Good Healthy School approach, it is also assumed that improvements in direct outcomes and mental health will have a positive long-term effect on pupils’ educational outcomes (e.g. academic performance, learning behaviour). Finally, the intervention model includes a number of factors that have been shown in previous studies to be relevant to intervention effectiveness. In addition to ‘traditional’ measures of implementation fidelity, such as adherence, dosage or acceptability [24], we included further measures such as health-promoting leadership or readiness for change [25]. Table 1 provides an overview of the measurements.

**Table 1 Tab1:** Overview of study measurements

Construct	Measure	Metric	Method of aggregation	Source
Mental and behavioural problems	SDQ [26]	Ordinal	Sum score	PU, T, PA
Emotion related knowledge	Self-developed	Nominal	Sum score	PU
Social-emotional skills	FEESS 1–2 [27]	Nominal	Sum score	PU
Diagnostic skills	COAKTIV [28]	4-point scale	Mean	T
Classroom disruption	FASS [29]	5-point scale	Sum score	T
Mobbing	PISA [30]	4-point scale	Sum score	T
Classroom climate	QuaSSU [31]	4-point scale	Sum score	T
Health Promoting School mission	Extended SEP scale on health promotion [32, 33]	5-point scale	Mean	T
Organisational commitment	COMMIT [34]	4-point scale	Mean	T
Academic performance	Adapted by [35]	5-point scale	Mean	T, PA
Learning behaviour	Adapted by [35]	5-point scale	Mean	T, PA
Implementation of MindMatters teaching module	Adapted by [36]	Mixed	Weighted sum-score	T
Implementation of MindMatters school development module	Self-developed	Mixed	Weighted sum score	T

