Statistical analyses will be performed using the latest version of STATA (Stata Corp., College Station, TX, USA). The main analysis will consist of a multilevel regression in which the primary outcomes are predicted at the pupil level using group status (intervention versus control group), controlled for baseline condition. Group status will be included in the model as a fixed effect and a random intercept will be provided for the cluster variables (study region, school, class). Furthermore, all variables with differences between the intervention and control group at baseline will be included in the model. Further mediation analyses will investigate which mediating mechanisms can be identified. It is assumed that the change in mental health outcomes is caused by improvements in proximal (i.e. direct and class/organisational) outcomes. This requires that the group status (i.e. the intervention) is correlated with the proximal outcomes and that the proximal outcomes are significantly related to the distal outcomes. Mediation effects will be examined using the Baron and Kenny partial correlation analysis approach and structural equation models [44, 45]. Moderator analyses will also examine which school-level factors (e.g. size, social gradient) are associated with or influence the impact of MindMatters. Moderator effects are tested using interaction terms in the regression model. The analysis will first be conducted according to the intention-to-treat principle and additionally compared with a per-protocol analysis. Analysis sample 1 includes all those for whom data are available at both measurement points (complete case analysis, as randomised). Analysis sample 2 includes all those reached at baseline (ITT as randomised). Analysis sample 3 includes all those with data available at both measurement points, and schools without intervention are included in the control group. Multiple imputation is used for missing values. To ensure the methodological quality of all analyses, statistical advice is provided by an independent institute.

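### The mediation analysis rests on two associations read at one post-test, so neither Baron-Kenny steps nor structural equation models can separate mediation from a shared cause, a shared rater or reversed order

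*Protocol article*

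**What the plan says.** Under Data collection, management and statistical analysis, the article first states a causal premise: "It is assumed that the change in mental health outcomes is caused by improvements in proximal (i.e. direct and class/organisational) outcomes". It then says what this requires, namely that "group status (i.e. the intervention) is correlated with the proximal outcomes and that the proximal outcomes are significantly related to the distal outcomes". The methods follow: "Mediation effects will be examined using the Baron and Kenny partial correlation analysis approach and structural equation models".

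The design is a "two-arm cluster-randomised controlled superiority trial (CRCT) with baseline and post-measurement", and under Study design "Data will be collected at baseline and again 18 months after the start of the intervention". Pupils and teachers are surveyed on both occasions, parents at post-test only.

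The Measures section describes an order in time. Of the mental health effects it says that "these effects are preceded by direct effects at the individual level, such as knowledge or skills", and it places classroom and organisational effects before them too.

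Table 1 gives the informants. The Strengths and Difficulties Questionnaire (SDQ) is completed by pupils, teachers and parents. Emotion-related knowledge and social-emotional skills come from pupils. Diagnostic skills, classroom disruption, bullying, classroom climate, school mission and organisational commitment come from teachers.

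**The concern.** Randomisation protects two of the three relations in a mediation model: group to mediator and group to outcome. It does not protect mediator to outcome. That relation has to be argued for, either by time order or by an assumption that nothing else drives both variables.

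The design cannot supply time order. Baseline precedes the intervention, so the post-test is the only occasion on which either a mediator or an outcome can show an effect of it. The intervention model asserts that proximal change comes first, but no wave observes this.

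The measures also give several reasons to expect a residual correlation without mediation:

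- **Shared rater.** Every pupil- or teacher-rated proximal outcome has an SDQ version from the same informant.
- **Shared content.** The Discussion concedes that the SDQ contains items on classroom disruption, and classroom disruption is itself a proposed proximal outcome.
- **Shared context.** A difficult class can worsen both climate ratings and SDQ scores.

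At stake is the abstract's promise of insight into how proximal and distal outcomes are related. A positive result could not be told apart from these alternatives.

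**Working it through.** **The plan's own figures.** No figure is stated for the mediation analysis. The sample size supplies the number of pupils per school, so it was reproduced first. The control prevalence is not stated; 14% against 10% is an assumption found by back-solving.

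- (1.96 + 0.842)² × (0.14×0.86 + 0.10×0.90) / 0.04² = 7.849 × 0.2104 / 0.0016 = 1032.1, so 1033 per arm and 2066 in total, as stated.
- (1 + 14×0.01) × 2066 = 2355, as stated.
- 2355 / 0.9 = 2617, against 2615 stated, which is a rounding difference.
- 2355 / 40 schools = 58.9, taken as 59 pupils per school.

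The sample size is not at issue here.

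**Simulation.** There were 600 simulated trials per setting, each with 40 schools of 59 pupils and two waves. Baseline mediator and baseline outcome were covariates, and tests were school-cluster-robust on 38 degrees of freedom. The true mediator-to-outcome path was zero throughout.

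Inputs from the article are 40 schools and, for the mediator, d = 0.5 for knowledge ("medium effects can be expected at the level of knowledge for primary school pupils") and d = 0.1 to 0.3 for competence. Assumed, because the article does not give them, are the residual mediator-outcome correlation at post-test (0 to 0.3), a school ICC of 0.05 unless noted, and direct effects on the outcome of 0 to 0.3. Effects are in units of the post-test SD given baseline. Monte Carlo standard error is at most √(0.25/600) = 2 percentage points.

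Share of trials in which mediation would be declared:

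| Setting (no true mediator effect) | Two listed conditions | Plus significant total effect | Product test of indirect effect |
|---|---|---|---|
| Correlation 0, mediator d 0.3 | 4.5% | 0.5% | 2.5% |
| Correlation 0, mediator d 0.5 | 6.3% | 0.8% | 5.0% |
| Correlation 0.05, d 0.3 | 52% | 2.5% | 41% |
| Correlation 0.10, d 0.3 | 92% | 3.5% | 88% |
| Correlation 0.10, d 0.1, ICC 0.01 | 48% | 1.8% | 44% |
| Correlation 0.30, d 0.5 | 100% | 4.8% | 100% |
| Correlation 0.10, d 0.3, direct effect 0.2 | 96% | 62% | 91% |
| Correlation 0.10, d 0.3, direct effect 0.3 | 96% | 89% | 90% |
| Reversed: group to outcome 0.3, outcome to mediator 0.5 | 36% | 36% | 38% |
| Reversed: group to outcome 0.3, outcome to mediator 0.3, plus group to mediator 0.2 | 92% | 89% | 93% |

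The product column stands in for what a structural equation model would test on the same two waves.

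**Hand check of two rows (d 0.3, ICC 0.05).**

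- Group to mediator: SE = √[(4/40) × (0.05 + 0.95/59)] = 0.0813, so 0.3/0.0813 = 3.69. Against a critical value of 2.02 the power is about 0.95.
- Mediator to outcome at correlation 0.05: the spurious slope is 0.95 × 0.05 = 0.0475, with SE about √[(1 + 58×0.05²)/2360] = 0.022. The ratio is 2.16 and the rejection rate about 0.55.
- The product is 0.95 × 0.55 = 0.52, matching the simulated 52%.
- At correlation 0.10 the slope is 0.095, the ratio about 4.3 and the rejection rate about 0.99. The product is 0.94, against 92% simulated.

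The reason is plain: with about 2,360 pupils, even a very small shared residual correlation is significant, so the second condition screens out little.

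**The case against.** Several points on the other side are fair.

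- **Structural equation models are also named.** A reader might infer that the plan yields no estimate or interval for the indirect effect. That applies to the Baron-Kenny steps only; a structural equation model can supply both. It does not remove the confounding, as the 88% at correlation 0.10 shows.
- **Clustering.** A reader might infer that the mediation models ignore schools and classes. The article does not say so. It specifies random intercepts for the main analysis and is silent on the level structure of the mediation models, which a condensed article may leave to the full plan. No finding is made on this.
- **Requirements are not a decision rule.** The wording gives necessary conditions for an assumed model; it does not say that mediation is declared whenever both hold. That stands. But these are the only conditions given, and the article states no assumption or check on mediator-outcome confounding.
- **The full Baron-Kenny sequence includes a significant total effect.** It does, and this largely protects against false mediation when the intervention does nothing to the outcome. The article's list omits this step. The protection also fails where a mediation claim is most likely to be made, when the intervention works by some other route.
- **A better model does not cure confounding.** Correct. The simulation already adjusts for both baselines. The sensitivity analysis, the cross-informant pairs and the wording are what bear on this problem.
- **Multiple informants are available.** They are, and the Discussion describes a multi-informant approach, but the analysis section does not say which pairs will be used.

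**Conclusion.** The point holds as a limit on what the mediation analysis can show. With one post-baseline wave, neither named method can distinguish mediation from a shared cause, a shared rater or reversed order, and the causal premise "It is assumed that the change in mental health outcomes is caused by improvements in proximal" outcomes cannot be tested by the two associations listed.

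Its size depends on assumptions outside the article. With residual correlations of 0.05 to 0.10 and a mediator effect of 0.3, the two conditions are met in about half to nine-tenths of trials without any mediator effect. With a total-effect step the rate is about 5% or less if the outcome is unchanged, and 62-89% with a direct effect of 0.2 to 0.3. With no shared residual cause it is about 5%.

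A reader might infer that the trial will report false mediation at one of these rates. The article does not support that, because it gives no residual correlations. The conclusion is that it can. Nor is the trial's main result in doubt: mediation is a further analysis, and the randomised primary comparison does not depend on it.

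**What to change.** 1. Drop the Baron-Kenny significance steps. Make the structural equation model already planned a multilevel one (school and class), adjusted for baseline mediator and baseline outcome. Report the indirect effect with a school-level bootstrap or Monte Carlo interval.
2. Take mediator and outcome from different informants where both exist, for example teacher-rated climate with pupil SDQ, or pupil-rated skills with teacher SDQ. Parent SDQ is post-test only, so a pair using it cannot be adjusted for its own baseline. Cross-informant pairs remove the shared rater, not shared class context.
3. State the assumption of no unmeasured mediator-outcome confounding. Add a sensitivity analysis showing how large a residual correlation would remove the indirect effect.
4. Label mediation exploratory, say that two waves cannot show time order, and report results as consistent with mediation, not as causal.

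No new data are needed. The cost is modest extra programming and a weaker mediation claim.

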The main limitation of this study is the assessment via self-reports. There is an increased risk of systematic bias, such as recall bias. Especially in younger children, challenges such as limited language and cognitive abilities or comprehension difficulties must be taken into account [50], although self-reports have previously been shown to be reliable and valid measures of mental well-being in adolescents. In addition, the power calculation was made a priori without information on the ICC estimate for mental disorders in children. Post hoc, the ICC for the SDQ could be determined from the pilot data and it was found that the ICCs ranged from *p* = 0.03 (hyperactivity) to *p* = 0.07 (behavioural problems with peers), indicating a severe underestimation of the ICCs for the SDQ. Furthermore, the SDQ might not be an adequate proxy for mental disorders, as it includes, for example, items for classroom disruption and prosocial behaviour. Although the trial might therefore not be suitably powered to detect small intervention effects, type I error inflation might be cushioned by the large number of clusters at the classroom level.

Also, as participation is voluntary, non-compliance could become an issue. Teachers are expected to teach the prepared modules and excercises independently of their teaching responsibilities and may find this an additional burden. These classes may discontinue participation in MindMatters early. Another limitation to the implementation of the intervention is the significant additional burden placed on schools by the Corona pandemic. As health promotion is not legally anchored in schools, this could lead to limited resources being invested in school health interventions [51]. As a result, a certain selection bias in school participation cannot be ruled out. Finally, this study is conducted in three German federal states, and conclusions cannot be directly transferred to other federal states due to the differences in the education systems.

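### Analysis sample 3 counts intervention schools that did not implement as controls, so the comparison set against intention-to-treat is as-treated rather than per-protocol

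*Protocol article*

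**What the plan says.** All of the analysis rules are in the section on data collection, management and statistical analysis. The order is set first: "The analysis will first be conducted according to the intention-to-treat principle and additionally compared with a per-protocol analysis". Three samples follow.

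- Sample 1 takes pupils with data at both time points and is marked "complete case analysis, as randomised".
- Sample 2 takes everyone reached at baseline and is also marked as randomised.
- Sample 3 carries no such mark: "Analysis sample 3 includes all those with data available at both measurement points, and schools without intervention are included in the control group".

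The main model regresses the pupil outcome on group status, controls for baseline condition and adds variables that differ between the groups at baseline.

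On adherence, the Discussion says that "as participation is voluntary, non-compliance could become an issue". It adds that teachers "may find this an additional burden", and that classes may stop early.

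**The concern.** A per-protocol set normally leaves out units that did not adhere. Sample 3 keeps them and counts them in the other arm. The two groups then differ by what the schools chose or managed to do, and no longer by allocation alone. Schools under more strain may be less likely to implement, and their pupils may differ for reasons that have nothing to do with MindMatters.

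At stake is how the planned comparison with intention-to-treat will be read. A larger effect in sample 3 could be taken to mean that the programme works where it is delivered, which is close to the fifth hypothesis on implementation quality. The Discussion claims high internal validity from randomisation and wants the results to help funders and decision-makers. Sample 3 does not have that validity.

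**Working it through.** **Reading the clause.** Samples 1 and 3 both take pupils with data at both time points. If the schools without intervention were only the randomised controls, the two samples would be identical. The clause therefore has an effect only if it moves intervention schools that did not implement. Sample 3 is also the only sample left to serve as the per-protocol analysis announced just before.

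**Inputs.** The sample size section gives 20 + 20 schools, a planning ICC of 0.01 and (1 + 14 × 0.01) × 2066 = 2355 analysed pupils, which I reproduce; 2355 / 40 is about 59 per school. The Discussion gives pilot ICCs of 0.03 to 0.07. The document gives no non-implementation rate and no outcome gap, so both are assumptions below.

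**Arithmetic with no true effect.** Let higher scores be worse and both randomised arms have mean 0. A share s of intervention schools does not implement, and their mean is D above that of the implementers. D is the gap that remains after baseline adjustment.

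- Implementers: −sD. Non-implementers: (1 − s)D.
- Enlarged control group: s(1 − s)D / (1 + s).
- False benefit in sample 3: sD + s(1 − s)D / (1 + s) = 2sD / (1 + s).
- False benefit if the schools are only excluded: sD.
- Ratio of the two: 2 / (1 + s).

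| Non-implementing | D (SD) | Sample 3 | Exclusion only | Ratio |
|---|---|---|---|---|
| 2 of 20 | 0.1 | 0.018 | 0.010 | 1.82 |
| 4 of 20 | 0.2 | 0.067 | 0.040 | 1.67 |
| 6 of 20 | 0.3 | 0.138 | 0.090 | 1.54 |

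If D is negative, the same sizes appear as harm. The protocol's assumed competence effects are d = 0.1 to 0.3.

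**Is the gap feasible?** It implies between-school variance of at least s(1 − s)D². For 4 of 20 and 0.2 SD this is 0.2 × 0.8 × 0.04 = 0.0064. Treating the ICCs as school-level, that fits within 0.01 but needs a correlation of √(0.0064 / 0.01) = 0.80 between non-implementation and outcome. At ICC 0.03 it needs 0.46, and at 0.07 it needs 0.30. For 6 of 20 and 0.3 SD the variance is 0.3 × 0.7 × 0.09 = 0.019, which is not possible at the planning ICC.

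**With baseline adjustment made explicit.** A simulation under no effect used 20,000 runs per scenario, 20 + 20 schools, about 59 pupils each, and school-mean analysis of covariance on baseline with an assumed baseline-to-post school correlation of 0.5. It assumed 20% non-implementation and a correlation of 0.5 between the tendency not to implement and a worse school outcome.

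| ICC | Mean false benefit, sample 3 (SD) | False-benefit rate, sample 3 | False-benefit rate, as randomised |
|---|---|---|---|
| 0.01 | 0.025 | 6.8% | about 2.5% |
| 0.03 | 0.041 | 8.4% | about 2.5% |
| 0.07 | 0.059 | 9.5% | about 2.5% |

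Over 10–30% non-implementation and correlations of 0.3 to 0.8, the false benefit runs from 0.009 to 0.126 SD and its rate from 3.5% to 28%. At correlation 0 there is no bias. At −0.5 and 20% non-implementation it turns into apparent harm of 0.026 to 0.058 SD.

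**The case against.** The strongest reply is that nothing essential depends on sample 3. Intention-to-treat comes first, samples 1 and 2 stay as randomised, and sample 3 is defined openly. This stands, and it limits the severity. A reader might infer that the trial's main conclusion is at risk; the document does not support that. Nor does it attach the words per-protocol to sample 3. The link follows by elimination, and how the result will be published is not stated.

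The second reply is that the model adjusts for baseline, and that readiness for change and health-promoting leadership are recorded in both groups. This also stands in part. Only the gap left after adjustment can bias sample 3, and the simulated values are smaller than the larger entries in the first table. Adjustment removes the bias only if it captures all relevant school differences, which cannot be assumed.

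Third, a reader might infer that the bias most likely favours MindMatters. The Discussion links non-compliance to burden but says nothing about pupils' outcomes in such schools, so the direction is open. If there is a true effect, counting partly exposed schools as controls would also dilute it. A reader might also suppose that moving schools doubles the bias compared with excluding them. The ratio 2 / (1 + s) is 1.5 to 1.8 in the cases shown.

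**Conclusion.** The point holds as a moderate error in a secondary analysis. Sample 3 is an as-treated comparison of completers, and it stands where the protocol announces a per-protocol analysis. It is biased whenever non-implementing schools differ in outcome after adjustment, and the sign of the bias follows the sign of that difference. In the illustration the false benefit is 0.067 SD, about two thirds of the smallest assumed competence effect (0.067 / 0.1), of which 0.04 SD would remain under simple exclusion. These sizes depend on the assumed non-implementation rate and residual gap. That the comparison is no longer randomised depends on neither.

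**What to change.** Delete the reassignment clause and state that every school is analysed in its randomised arm in all analyses.

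If an effect in implementing schools is wanted, estimate a complier average causal effect with allocation as the instrument and school-clustered standard errors. This needs two further statements:

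- an implementation threshold, built on the lesson and school-development documentation already collected and fixed before outcomes are compared by arm;
- the exclusion restriction, that allocation has no effect on pupils in schools below the threshold. Delivery is flexible and implementation is scored on a continuum, so this needs a justification.

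An exclusion-based per-protocol set may be kept, but it retains (1 + s) / 2 of the bias, 55% to 65% in the cases above. It should be labelled non-randomised and exploratory. If sample 3 itself is kept, call it as-treated and exploratory. Neither should be read as confirming or strengthening the intention-to-treat result.

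The cost is a few sentences and one additional model, with no new data. The complier estimate has a wider interval and relies on an extra assumption.
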